## Methods/Design

### Setting and participants

The study will take place at one FQHC whose mission is to provide a community medical home through accessible, compassionate, and quality healthcare services. The center offers a full range of comprehensive primary and preventive services, including childhood immunizations and physical exams, adult physical exams, management of chronic illnesses, family planning services, maternity care services, and health education promotion. In 2015, the center served 11,895 unduplicated patients for a total of 25,362 patient visits. Of those patients, 90% were Hispanic and the majority did not speak English. There are currently five physicians and four mid-level providers (physician assistants and nurse practitioners) working at the center.

The target enrollment is 150 patients over the 24-month enrollment period. All adult primary care patients at the center will be asked to participate in screening for depression with the iPad Depression Screening application (universal screening). After being informed about the expectations for participation in the study and the compensation payments, it is expected that a minimum of 2–3 patients per week will agree and be enrolled in the study. Patients who meet study inclusion criteria will be enrolled on a first-come, first-serve basis until the target of 150 patients is reached. The study protocol was reviewed and approved by the Institutional Review Board of the University of Texas at Arlington. All patients will provide written informed consent to participate.

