The primary outcome for Aim 2 is the change from baseline to 12-month scores on the PHQ-9 depression measure (dependent variable) for patients enrolled in MBIC. Outcomes will then be compared between and the MBIC + DEF and the MBIC + SE intervention groups.Current literature on the PHQ-9 suggests that a 5-point drop in mean depression scores is an indication of a clinically significant response to treatment [59]. The DEF group is hypothesized to have a greater proportion of the group report a clinically significant decrease in depression scores (5-point decrease in PHQ-9 scores) when compared with the SE group.The U.S. Department of Health and Human Services suggests that the objective of collaborative care research should be to have 40% or more of the patients realize a 50% or greater reduction in depression scores [60].

The evaluation of Aim 3 will examine the feasibility of universal screening for depression using the iPad Depression Screening and Monitoring technology, and will be measured by its positive predictive value, clinical utility, ease of use, and acceptability of routine use among clinicians:Quantify the number of adult patients screened per month and if the score is being placed in the EHR.Determine if the iPad Depression Screening application changes PCP approach to the diagnosis and treatment of depression as measured by the number of patients with a new depression diagnosis as a percentage of the total number of adult patients seen in the clinic compared to a matched set the year prior to the study based on EHR (baseline data).Quantify changes in the number of patients with a depression diagnosis being treated with antidepressants by the PCP as a percentage of the total number of patients seen in the clinic compared to a matched set the year prior to the study based on EHR (baseline data).

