## Discussion

This study protocol describes a randomized control trial testing a culturally adapted depression education intervention designed to reduce stigma and increase disease literacy. The target of the three-part design is to improve detection, diagnosis, and increasing uptake in depression treatment among Hispanics in an integrated care model in a community-based health center. This study addresses the need for both identification and elimination of the barriers to treatment for the most common mental health condition affecting Hispanics. Various other design options were discussed, including testing the *fotonovela* as a discrete intervention, without the context of integrated care. However, with the U.S. Preventive Services Task Force recommendation for universal screening for depression in primary care settings and the emphasis on systems to address positive screens [61], the rationale for testing an innovative technology to facilitate screening and implementing an evidence-based treatment model for which there is a lack of studies among minority populations offers a greater opportunity to translate established research into clinical practice. The rationale for designing a complete intervention, while still testing a specific element for which cultural values about mental health may be distinct, appears scientifically feasible, and shows scientific promise.

The strengths and weakness of using a SE control group were carefully considered prior to selection. The primary benefit of the SE control group is that it ensures a comparable contact across the two interventions. As a result, a significant effect observed in the *fotonovela* condition cannot be attributed to differences in contact or participation outcome expectations. A potential concern with the control group is a threat to internal validity due to lack of treatment fidelity and interventionist allegiance. To reduce these concerns, the SE intervention will be manualized (based on NIMH education materials) and intervention fidelity procedures will be the same across the two interventions.

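### Aim 3 asks whether the iPad application changes diagnosis and treatment but compares only with a matched set from the year before, which cannot separate a background trend from the programme's effect

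*Protocol article*

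**What the plan says.** In the Analysis section, one evaluation item for Aim 3 is worded as a question about effect: "Determine if the iPad Depression Screening application changes PCP approach to the diagnosis and treatment of depression". It is measured by new depression diagnoses "as a percentage of the total number of adult patients seen in the clinic compared to a matched set the year prior to the study", with the earlier figures taken from the EHR. The next item, "Quantify changes in the number of patients with a depression diagnosis being treated with antidepressants by the PCP", uses the same prior-year comparator.

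The setting offers no other contrast. Under Setting and participants: "The study will take place at one FQHC", and "All adult primary care patients at the center will be asked to participate in screening for depression". The Analysis section assigns the randomised comparison to Aims 1 and 2. The only monthly quantity named for Aim 3 is the number of adults screened, not the diagnosis rate. The Discussion gives part of the rationale for the design as "with the U.S. Preventive Services Task Force recommendation for universal screening for depression in primary care settings".

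**The concern.** The question is about cause, but the only comparator is historical. If the proportion of adults newly diagnosed was already moving for reasons outside the study, the comparison with the prior year counts that movement as change due to the application. Matching does not help, because every matched record, whatever it is matched on, still comes from the earlier year.

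The same applies to the antidepressant measure. At stake is what can be concluded from these two items of Aim 3. A clinic or funder reading the result as evidence that iPad screening changed practice could be reading some mixture of drift and effect, in unknown proportion.

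**Working it through.** The protocol gives no rate, sample size or power for Aim 3, so there is no stated figure to reproduce. The check is one of design logic, followed by an illustration on assumed inputs.

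**Design logic.** Comparing the study period with the year before, the observed difference is

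(effect of the programme) + (background change between the periods) + (residual difference in patient mix).

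Matching can reduce the third term. The first two are aligned in time. With one clinic, all adults offered screening and no earlier baseline years, the comparison as stated cannot separate them.

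The first term is itself composite. The Measurement-based integrated care section adds a depression care manager, and the Discussion adds training of providers and staff in treatment guidelines. Both belong to the same project as the screening.

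**Illustration: how often drift alone would look significant.** Inputs:
- Study-period adults n1 = 8,000. Assumed: Setting and participants gives 11,895 patients in 2015 without the adult share.
- Prior-year rate p0 = 5%. Assumed.
- Background rise 10% per year, period midpoints one year apart, so p1 = 0.05 × 1.10 = 5.5%. Assumed.
- Screening effect zero.
- Comparator size n0 = 1,000, 2,000 or 8,000. The article does not say how large the matched set is.

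Formula: d = p1 − p0 = 0.005; SE = √[p1(1 − p1)/n1 + p0(1 − p0)/n0]; P(p < 0.05) = Φ(d/SE − 1.96) + Φ(−d/SE − 1.96).

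| n0 | SE | d/SE | P(p < 0.05) |
|---|---|---|---|
| 1,000 | 0.00735 | 0.68 | 0.10 |
| 2,000 | 0.00550 | 0.91 | 0.15 |
| 8,000 | 0.00353 | 1.42 | 0.29 |

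Sensitivity, each against a nominal 0.05:
- With 8,000 per period, a 5% rise gives 0.11 and a 15% rise gives 0.56.
- With a 15% rise and comparators of 1,000 or 2,000, the figures are 0.17 and 0.27.
- With a 10% rise and equal periods: 0.14 (3,000 adults, 5% rate), 0.16 (6,000, 3%) and 0.53 (10,000, 8%).

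The answer depends heavily on inputs that the document does not give.

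**How much history is needed to estimate a trend.** At 8,000 × 0.05 / 12 ≈ 33.3 new diagnoses a month, the standard error of the annual log-trend is 1/√[33.3 × Σ(t − t̄)²], with t in years:
- 12 months: Σ(t − t̄)² = 0.993, SE = 1/√33.1 = 0.174, 95% half-width 1.96 × 0.174 = 0.34.
- 36 months: Σ(t − t̄)² = 26.98, SE = 1/√899 = 0.033, 95% half-width 1.96 × 0.033 = 0.065.

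On these assumptions one pre-study year fixes the yearly trend only to about ±34%, and three years to about ±7%. Splitting the planned prior year into months would therefore not be enough.

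**The case against.** Aim 3 is labelled feasibility. Its items mostly quantify, and the Analysis section names no test, hypothesis or power for it. It is therefore fair to say that significance rates describe a test the plan does not state. This stands, and the rates above are illustrative only. It does not remove the problem, because a difference reported descriptively carries the same bias and the stated question is whether the application changes practice.

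The matched set is undefined in a condensed article. A reader might infer that it is a small subset matched on patient characteristics, set against all adults. The text does not say so, and the definition may sit in a fuller document. The point does not rest on that reading: no choice of matching variables within the prior year removes a calendar trend.

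A reader might also infer that diagnosis was already rising because of the national screening recommendation. The Discussion cites that recommendation as rationale for the design. Nothing shows a rise at this clinic. It makes outside pressure plausible and no more.

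Materiality can be questioned too. The assumed rises of 5% to 15% move a 5% rate by only 0.25 to 0.75 percentage points. The protocol screens all adults at a PHQ-9 cut-off of 5, cites a 27% depression prevalence in a national Hispanic sample, and expects to find many unrecognised cases. If screening has a large effect, drift of this size would be unlikely to decide the conclusion. That is a fair limit on how serious the point is.

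Finally, one might think that adjusting for trend would isolate the iPad. It would not, because the care manager, integrated care and provider training accompany the screening.

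**Conclusion.** The concern holds in limited form. Aim 3 fixes a comparison that cannot answer its own question, because a prior-year matched set at a single clinic leaves any background trend mixed with the effect of the programme. This follows from the design as stated and needs no assumed numbers.

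The size of the bias is unknown. The illustrative 10% to 29% rests on an assumed adult count, base rate, 10% yearly rise, one-year gap between midpoints and zero screening effect, and on a test that the plan does not name. If the full 24-month enrolment period were set against the prior year, the midpoints would lie about 1.5 years apart and the same yearly trend would weigh more. The document does not support the stronger statement that Aim 3 will credit the iPad with a change that did not occur.

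The randomised comparisons under Aims 1 and 2 are unaffected, so this is a minor-to-moderate improvement.

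**What to change.** Use the EHR extraction already planned, with a longer look-back. For all adults, take monthly counts of adults seen, new depression diagnoses and antidepressant treatment, for about three pre-study years (or as many as the EHR reliably holds) and throughout the study. Fit a segmented (interrupted time series) regression, and report the change in level and slope at the start of screening, with its confidence interval, in place of the comparison with the prior-year matched set.

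Reword the Aim 3 item so that any change is attributed to the whole programme (screening, care manager with integrated care, and provider training), not to the iPad application alone.

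Cost: a longer retrospective extraction and some analysis time, with no patient contact. The interval will be wider than for a simple before-and-after difference, because the trend must be estimated. The approach also depends on how far back the EHR goes and whether coding was stable, which the document does not state. If reliable history is too short, keep the prior-year figures as description and drop the wording that the application changes practice.

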The scope of this project is ambitious, in that we aim to change provider behavior and screen all adult primary care patients for depression. With that in mind, we realize that we will identify a large number of patients whose depression was previously unrecognized. For busy primary care practitioners, this will undoubtedly increase their workload. However, with the support of the DCM and MBIC, the burden of systematic measurement, education about the disease and tracking of outcomes will be reduced. Additionally, we look to offset the potential treatment burden by training the PCPs and their clinic staff in evidence-based treatment guidelines, and through the use of the iPad Depression Screening and Monitoring application. It is anticipated that the recognition and treatment of depression will improve other co-morbid chronic disease and ultimately reduce the overall burden of disease management on the primary care practice.

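### Aim 3's two before-after rates use different denominators, the antidepressant rate cannot by itself show a change in prescribing, and the comparison cannot isolate the iPad application

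*Protocol article*

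**What the plan says.** The Aim 3 items at the end of the Analysis section of the protocol article include two before-after measures from the electronic health record (EHR).

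- **Diagnosis.** The purpose is to "Determine if the iPad Depression Screening application changes PCP approach to the diagnosis and treatment of depression". It is measured by patients with a new depression diagnosis, "as a percentage of the total number of adult patients seen in the clinic".
- **Antidepressants.** The task is to "Quantify changes in the number of patients with a depression diagnosis being treated with antidepressants by the PCP", expressed "as a percentage of the total number of patients seen in the clinic".

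Both are "compared to a matched set the year prior to the study based on EHR (baseline data"). The matching factors are not given.

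Under Setting and participants, the clinic's services are described as "including childhood immunizations and physical exams, adult physical exams" and further adult and maternity care. Universal screening with iPad technology offers the screen to adults only.

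Other components belong to the same project. The depression care manager (DCM) confirms the diagnosis by clinical interview (Randomization) and works with the primary care provider (PCP) on treatment plans that may include medication (Measurement-based integrated care). All enrolled patients receive MBIC (Intervention). The Discussion adds "training the PCPs and their clinic staff in evidence-based treatment guidelines".

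**The concern.** Three separate problems affect what Aim 3 can conclude.

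1. **Base.** One rate is per adult and the other, read literally, is per patient of any age. They cannot be set side by side, and the second can change because the clinic saw relatively more or fewer children.
2. **Meaning.** The antidepressant item is the only treatment measure under Aim 3, and the stated question covers treatment as well as diagnosis. A rate per patient seen combines how many are diagnosed with how many of those are treated. Universal screening is expected to raise the first, so a rise in the rate is not evidence about the second.
3. **Attribution.** The question names the application as the agent of change. A comparison with the year before the study compares everything the project brought in with whatever was there before. Matching patients between years does not separate the app from the care manager, MBIC or the training.

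At stake is a report that PCPs changed how they treat depression when only detection changed, or one that credits the screening tool with the effect of a larger programme.

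**Working it through.** Aim 3 states no target, sample size or expected rate, so there is no figure of the plan to reproduce. The check is algebraic, with illustrative inputs.

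**Set-up.** Let *a* be the adult share of patients seen, *d* the proportion of adults with a depression diagnosis, and *t* the proportion of those who are on an antidepressant from the PCP. Assume that the treated patients counted are adults. Then:

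- antidepressant rate as written = *a* × *d* × *t*
- rate per adult seen = *d* × *t*
- rate among diagnosed adults = *t*

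The article gives none of *a*, *d* or *t*. It reports 11,895 patients in 2015 without an adult/child split. All values below are assumptions.

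**Detection alone.** Let *d* go from 10% to 20%, with *t* fixed at 30% and *a* = 0.65.

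| Denominator | Before | During | Ratio |
|---|---|---|---|
| All patients seen | 0.65 × 0.10 × 0.30 = 1.95% | 0.65 × 0.20 × 0.30 = 3.90% | 2.00 |
| Adults seen | 0.10 × 0.30 = 3.00% | 0.20 × 0.30 = 6.00% | 2.00 |
| Diagnosed adults | 30% | 30% | 1.00 |

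The ratio of 2.00 in the first two rows is the same for every adult share tried from 0.5 to 1.0, for *d* going from 5% to 10% or from 10% to 20%, and for *t* of 30% or 50%. Restricting the denominator to adults therefore does not remove the dependence on detection. Only dividing by diagnosed patients does.

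**Detection up, treated share down.** With *a* = 0.65, *d* from 10% to 20% and *t* from 50% to 30%, the rate goes from 0.65 × 0.10 × 0.50 = 3.25% to 0.65 × 0.20 × 0.30 = 3.90%. It rises while the treated share falls by 20 percentage points. With *a* = 0.6, *d* from 5% to 15% and the same fall in *t*, it goes from 0.6 × 0.05 × 0.5 = 1.5% to 0.6 × 0.15 × 0.3 = 2.7%. With *t* held at 50%, it would reach 0.6 × 0.15 × 0.5 = 4.5%.

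**Child/adult mix alone.** With *d* = 10% and *t* = 40% in both years:

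- *a* from 0.60 to 0.70 moves the rate from 2.4% to 2.8%, a relative change of 0.70/0.60 − 1 = +17%.
- *a* from 0.65 to 0.60 moves it from 2.6% to 2.4%, a relative change of 0.60/0.65 − 1 = −8%.

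The rate per adult seen is 4.0% throughout.

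**Attribution.** No arithmetic applies. Of the components listed above, the training is aimed directly at PCP treatment, and the care manager takes part in both diagnosis and treatment planning. The article describes no period or group with the app but without these components, so nothing in the design separates them.

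**The case against.** The strongest reply has four parts.

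**A rate per population is a proper outcome for a screening programme.** If screening finds more cases and more clinic patients are treated, the rate should rise, and that rise is real. This stands: the rate should be kept. It does not answer the question about PCP approach. The neighbouring diagnosis rate does not fully resolve this either, because it counts new diagnoses per adult while the antidepressant rate counts treated patients with any depression diagnosis per patient seen. The treated share cannot be recovered by dividing one by the other.

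**The missing restriction to adults may be a slip.** Specific aim 3 concerns adult primary care patients, and the undefined matching might balance age between years. Both are possible, and the matching details may be in the full protocol. The printed denominators still differ. Age matching would not touch the dependence on detection.

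**The proportion among diagnosed patients has its own bias.** A PHQ-9 score of 5 or more counts as a positive screen, and 5–9 is graded mild. Screening may bring milder cases into the diagnosed group, and treatment may be counselling alone. The proportion could fall with no change in how similar patients are treated. This stands, and is why the two measures belong side by side.

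**The causal wording is attached to the diagnosis item, and MBIC reaches few patients.** The antidepressant item names no cause, but the causal question includes treatment and no other Aim 3 item measures it. Enrolment is 150 over 24 months; a year's 75 is 75/11,895 = 0.6% of the 2015 patient count, so MBIC's direct share may be small. The training and the care manager's contact after positive screens can reach further.

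A reader might also infer that counting children is what makes the rate rise with detection. The algebra shows otherwise: a constant child share lowers the level and leaves the ratio unchanged.

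**Conclusion.** The point holds in three separate parts.

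- The denominators of the two Aim 3 rates disagree as printed. If children are counted, a shift in the adult share from 0.60 to 0.70 alone changes the antidepressant rate by +17% in relative terms.
- The antidepressant rate is proportional to the diagnosed share. On its own it cannot show a change in PCP treatment approach, with or without children in the denominator.
- The prior-year comparison can describe the change that came with the whole programme, but not the contribution of the app.

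The proportionality is algebra and needs no assumed values. The percentages are illustrations only, and the fall in the treated share from 50% to 30% was chosen to show what is possible, not what is expected.

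Two stronger readings are not supported. A reader might infer that the prior year had no care manager, MBIC or training. The article does not describe prior-year care or date the training; their absence is inferred from the project introducing them. A reader might also infer that the trial's main results are at risk. Aim 3 is a non-randomised feasibility aim, and the comparison between the two education arms is unaffected.

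**What to change.** 1. Use adults seen as the denominator for both the diagnosis and the antidepressant rate, in both years.
2. Keep the antidepressant rate per adult seen, labelled as a population measure. Report beside it, for both years, the proportion of adults with a depression diagnosis who are prescribed an antidepressant by the PCP. State that this proportion may shift if screening brings in milder cases.
3. Word the question and conclusion as the change associated with the whole programme (screening, DCM and MBIC, and PCP training), not with the iPad application alone.

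The cost is slightly more analysis of EHR data and a narrower claim. Nothing in the conduct of the trial changes.

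Monthly rates with segmented regression are optional. So is separating PCP-entered from DCM-confirmed diagnoses, which depends on whether the EHR records the distinction; the article does not say.
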